| Planned use of linked data (if applicable): Data linkage to the ONS and Basic HES are required to define the primary and secondary outcomes in the study. The ONS mortality register will be used to define any outcomes which result in death, and also censor follow-up at death. Specific linkages required will include data and ICD-10 coded cause of death (see attached code lists). Linkages to Basic Inpatient HES will be combined with data from the ONS to define all other outcomes in the study. HES data will also be used to define patients’ eligibility for the study (e.g. previous CVD), and define the study population (e.g. ethnicity where unavailable in Primary Care records). Data required from Basic Inpatient HES will include primary diagnosis, secondary diagnosis, patient characteristics (e.g. sex, ethnicity), date of admission and date of discharge. All deaths and hospital admissions occurring after a patient’s index date will be included. A linkage to the Index of Multiple Deprivation is required to acquire patient level quintiles of multiple deprivation, to better define the sample population and use as a covariate in the prognostic modelling. |

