| Exposures, Outcomes and Covariates This study will examine the overall risk of harm from three types of cardiovascular medication: antihypertensives, statins and antiplatelets. ‘Harm’ will be defined by the outcomes listed in the table below, which will be examined both individually and as a composite outcome. The association between treatment and a positive and negative control outcome will also be examined to check the validity of the treatment effect estimates. Positive controls are outcomes know to be affected by treatment (e.g. cardiovascular disease) and negative outcomes are those known not to be affected by treatment.   \| **Variable** \| **Antihypertensive therapy** \| **Statin therapy** \| **Antiplatelet therapy** \| \| --- \| --- \| --- \| --- \| \| Exposure \| ACE inhibitors  Angiotensin II receptor antagonists  Calcium channel blockers  Thiazides and thiazide-like diuretics  Beta blockers  Alpha blockers  Centrally acting antihypertensives  Vasodilators  Renin inhibitors \| Statins \| Aspirin  Clopidogrel  Dipyridamole  Ticagrelor  Prasugrel \| \| Outcome (hospital admission or death due to) \| Falls  Fracture  Syncope  Hypotension (symptomatic)  Acute kidney injury  Electrolyte abnormalities*  Gout  Any adverse event \| Myopathy/muscle pain  Diabetes mellitus  Intracerebral haemorrhage  Cataract  Liver dysfunction  Dementia  Memory problems (including dementia)  Any adverse event \| Intracerebral haemorrhage  Gastrointestinal haemorrhage  Dyspnoea  Any adverse event \| \| Covariates (predictors of outcome and/or treatment) \| Age, sex, BMI, blood pressure, cholesterol, HbA1c, other prescribed medications, co-morbidities, social deprivation, previous adverse events, frailty and proximity to death. \| \| \|   *Defined as any (hyponatraemia, hypokalaemia, hyperkalaemia, hypomagnesaemia, hypophosphataemia hypercalcaemia or hyperuricemia)  All outcomes will be defined according to diagnostic and/or symptom codes, unless otherwise stated. Further sensitivity analyses will explore the impact of our definition of myopathy and muscle pain, focussing on formal diagnostic codes for myopathy only.  Our PPI engagement suggests some patients are concerned about side effects which will result in having to go to hospital, whilst others are more concerned about chronic conditions which affect their daily quality of life. The primary outcomes of this study will therefore be hospital attendance, defined according to ONS and Basic HES datasets. Sensitivity analyses will explore outcomes defined more broadly using primary care codes as well.  All published outputs from this work will be based on the outcomes as specified in this application. Further work with our patient and public involvement representatives will explore definitions of these outcomes and how they should be incorporated into the final calculators developed as part of the wider programme of work related to this project.  Each model will be derived pragmatically, using coded data routinely available in a primary care setting. Potential predictors will be selected based on previous literature and expert opinion.^30 31 44^ Predictors will be defined by codes in the primary care records, using code lists from previous studies (via [www.clinicalcodes.org](http://www.clinicalcodes.org)). Each model will also incorporate basic patient characteristics, blood pressure level, co-morbidities and frailty, estimated from the electronic frailty index. |

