| Data/ Statistical Analysis **Prognostic modelling**  ***Aim 1 – prognostic model derivation (primary analysis)***  Where feasible and appropriate, flexible parametric survival models will be derived in the CPRD GOLD for each outcome separately. Baseline survival over time will be estimated using the Royston-Parmar approach of restricted cubic splines on the cumulative log hazard scale. In contrast to Cox regression, this allows a smoothed estimate of the baseline survival function to be derived, and the time period of prediction to be varied, facilitating individualised risk prediction. For the primary analysis, a 10-year period of prediction will be considered. Further sensitivity analyses will be conducted examining a 5-year period. Where insufficient data are available, or modelling procedures become prohibitively complex (computationally), simpler approaches such as Cox regression will be considered.  Each drug class (prescribed in the 12 months prior to the index date) will be entered into the model as a binary variable to allow for multiple treatments to be considered in each model. Where appropriate, models will be constructed with all other variables entered as continuous (not categorised) variables, and potential non-linear trends will be examined. Transformations or fractional polynomials will be used if non-linear trends are detected. Where hazard ratios are not proportional, interactions of effects with time will be included. Further interaction terms, identified in an accompanying systematic review, accounting for treatment effects which differ across specific populations may be included. Where appropriate, models will be reduced and candidate predictors selected for inclusion based on p values of association. Time since cohort entry will be used as the underlying time function in each survival model.  In a further analysis, we will extend the modelling process as described above to account for competing risk of death from other causes. This will produce a model that predicts the risk of adverse events from cardiovascular treatment over time, in the real world where individuals might die from other causes and thus prevent cardiovascular treatment adverse events from occurring. We will again use a flexible parametric modelling framework to estimate the sub-distribution hazard and cause-specific cumulative incidence functions.^45^  Missing data will be handled, under a missing at random assumption, using multiple imputation (see below) followed by Rubin’s rules to combine parameter estimates across studies.  Where feasible and appropriate, each model will be internally validated using the bootstrap method, to allow optimism-adjusted estimates of calibration and discrimination performance to be obtained. Adjustment for overfitting will be undertaken using a uniform shrinkage factor identified from bootstrapping, followed by re-estimation of the cumulative baseline sub-distribution hazard function (and thus baseline cumulative incidence function) to maintain overall calibration between observed and predicted risks. Given the large sample size, overfitting is likely to be small (see sample size calculation above). If bootstrapping is computationally infeasible due to the large sample size, then a smaller random sample of the population will be used or alternative internal validation methods employed such as cross validation.  ***Aim 2 – prognostic model validation***  External model validation will be undertaken using data from CPRD Aurum. The accuracy of risk predictions from each model will be assessed with calibration plots and 5 and 10 years, calibration measures (slope, E/O statistics), measures of overall fit (using pseudo-R^2^ estimates) and discrimination measures (C-statistics and D-statistics).  ***Aim 3 – causal inference analysis***  For most of the outcomes described in this proposal, the association and magnitude of effect with treatment is not well defined in randomised controlled trials. We will therefore undertake causal inference work to examine whether modification of treatment could have an important impact on the risk of adverse events using two causal inference methods: propensity score matching and instrumental variable analysis.  For the propensity score analysis, eligible patients will be matched 1:1 at the index date using propensity scores, which indicate the likelihood a patient will be prescribed treatment on the basis of their known (pre-treatment) characteristics and other known information which might influence the decision to treat. Predictors of preventative drug prescription will be explored in a logistic regression model. Matched patients will be compared using the Cox proportional hazards models, but hazard ratios will only be adjusted by factors unbalanced at baseline which are not already included in the propensity score model. Time since cohort entry will be used as the underlying time function in each model.  For the instrumental variable analysis, GP’s previous antihypertensive prescribing preferences will be used as an instrument to predict the likelihood of actual treatment. Risk of adverse events will be estimated in patients attending a GP considered a high prescriber of preventative medication and compared to those attending a GP considered a low prescriber. If the results from the propensity score matching suffer from unmeasured confounding, they will differ from those of the instrumental analysis. If this is the case, these models will be refined with additional factors to achieve better adjustment and matching. Where all approaches provide similar results, we can be more confident that the findings are accurate and reliable.^46^  A similar approach will be applied to secondary outcomes, for example, memory loss which has been hypothesised as being linked with statins^47^ and is a concern of many patients in practice, but there is no evidence to support this association from trials.^48^ We recognise that the evidence base may change for some outcomes over the next few years, and so the need to test the associations between treatment and certain outcomes may change.  *Subgroup and sensitivity analyses*  Where possible and appropriate, analyses of treatment associations will be examined in subgroups of the population. These will include age, sex, baseline blood pressure and cardiovascular risk, by drug type/dose/intensity and past medical history. Subgroup definitions will be agreed by expert opinion or taken from an accompanying systematic review of previous trials, examining the same topic.  Sensitivity analyses will be undertaken examining risk models for outcomes defined according to both hospital and primary care records. We will also explore the impact of our definition of myopathy and muscle pain, focussing on formal diagnostic codes for myopathy only. Models utilising a 5-year follow-up will be examined as a further sensitivity analysis. The primary analyses will examine the association between treatment and outcomes, assuming treatments are not altered or modified in the future. Where possible, sensitivity analyses will examine treatment entered as time varying covariates, and censor patients who have treatments removed or switched following the index date. |

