| Limitations of the study design, data sources, and analytic methods This study focuses on potential harms from adverse events associated with preventative treatments for cardiovascular disease. Such outcomes may be less well recorded in routine electronic health records. For example, initial scoping work suggests the rate of falls documented in the CPRD is between 0.06-0.34% per 1000 person-months. These incidence rates may be less than those reported in smaller previous studies (0.15-6.40% per 1000 person-months) using different definitions, captured via detailed questionnaires and follow-up.^49-52^ Incidence rates are likely to be higher when linked data from HES and ONS are available.^53^ Missing data on certain outcomes may reduce the accuracy of the prognostic models, but should not bias the results provided the data are missing at random and not affected by whether patients are prescribed treatment. To minimise the risk of reporting bias, outcomes in the primary analysis will be defined according to hospital admissions documented in the HES or ONS.  The causal inference work will use an observational cohort design, and as such, there is an inherent selection bias of patients in both exposure and control groups. The impact of this bias will be limited by propensity score methods used to control for confounding, but this approach assumes that all confounding factors are measured and accounted for within the analysis. In the present study, we will examine the validity of this assumption by 1) using an instrumental variable (GP prescriber preference) and examining the association with the outcomes of interest and 2) by studying the impact of treatment on positive and negative controls: hospitalisation and/or death from cardiovascular disease and bowel cancer/COPD. We will conclude the assumption has been met if high GP prescribers have a similar association with outcomes and the treatment itself and treatment is shown to be associated with the positive control, but not the negative control.  *Strategy for dealing with potential errors resulting from multiple testing*  This study will examine multiple outcomes across 3 exposure variables. To avoid potential errors arising from multiple testing, a primary outcome has been clearly defined for each exposure variable. Secondary outcomes are also pre-specified. The primary outcome will be given priority in the final analysis write-up and any related reports and presentations.  Primary and secondary outcomes will be defined using data from Basic inpatient HES and ONS. Sensitivity analyses will explore analyses defining these outcomes using the above sources and read-coded primary care data. The accuracy of such outcome data has been examined previously in patients with acute myocardial infarction and whilst recording of risk factor and co-morbid information was consistent across primary care, hospital admissions and disease registry records, the crude incidence of acute myocardial infarction was underestimated by up to 50% if only one data source was used, compared with using all three sources.^53^ The use of linked CPRD data will ensure outcome data are ascertained accurately. |

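### For the causal analyses (Aim 3), previous adverse events are to be defined from primary care codes although the same kinds of event count as outcomes from HES and ONS; pre-exposure HES records should be added

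*Protocol*

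**What the plan says.** All points are from Part 2 of the protocol.

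- **Covariates.** The table in Exposures, Outcomes and Covariates has a row labelled "Covariates (predictors of outcome and/or treatment". Its list ends with "previous adverse events, frailty and proximity to death". The text below the table says "Each model will be derived pragmatically, using coded data routinely available in a primary care setting" and then "Predictors will be defined by codes in the primary care records, using code lists from previous studies".
- **Outcomes.** The same section says "The primary outcomes of this study will therefore be hospital attendance, defined according to ONS and Basic HES datasets".
- **Linked data.** Planned use of linked data requests HES inpatient records for outcomes. It adds "HES data will also be used to define patients’ eligibility for the study (e.g. previous CVD", and it allows ethnicity from HES where primary care lacks it. Deprivation comes from a linked index. The stated time window for admissions is after the index date.
- **Propensity score.** Under Aim 3 in Data/Statistical Analysis, the score may use known pre-treatment characteristics and "other known information which might influence the decision to treat". The same paragraph calls the inputs of the logistic model predictors of prescription. Amendment 2 adds a multivariable Cox model with pre-specified confounders and names no data source for them.
- **No record.** Plans for addressing missing data treats a co-morbidity with no record as absent.
- **Completeness.** The Limitations section reports that "the crude incidence of acute myocardial infarction was underestimated by up to 50% if only one data source was used". It expects event rates, with falls as its example, to rise once HES and ONS are linked. It also says that risk factor and co-morbidity recording agreed across sources.

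**The concern.** An admission for a fall, bleed or acute kidney injury is found in HES if it happens after the index date. The same admission before exposure enters the adjustment only if the GP coded it. Patients whose history was not coded are then grouped with patients who have none.

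A previous event of this kind plausibly predicts the next one and plausibly influences prescribing, so it is a confounder that Aim 3 needs to measure well. If it is half measured, adjusting for it or matching on it removes only part of the confounding, and a large sample does not help. At stake is whether the estimated harm of antihypertensives, statins or antiplatelets is biased by an amount similar to the effect sought.

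**Working it through.** **1. The effect the analysis is sized for.** Sample size considerations assumes a 10% higher rate, 90% power and alpha 0.05 (taken as two-sided). The Freedman formula gives (1.960 + 1.282)² × [(1 + 1.1)/(1 − 1.1)]² = 10.507 × 441 ≈ 4,634 events, the protocol's figure. With 0.5% per year over 10 years (the period is inferred), the control risk is 0.05 and the treated risk 1 − 0.95^1.1 = 0.0549. Then N = 4,634 / 0.0524 ≈ 88,384, against the stated 88,380. These figures are not in dispute. They set the yardstick: a rate ratio of 1.10, with a standard error of the log ratio of about 2/√4,634 = 0.0294.

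**2. Assumed inputs.** The documents give none of these except the 50%, which is their upper figure for acute myocardial infarction and is borrowed here.

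- 80% treated among those without the history
- history present in 5% to 10%
- odds of treatment with the history 0.25 to 0.5 times those without
- event risk 3 to 5 times higher with the history
- 50% or 80% of histories recorded, with no false records
- prescribing responds equally to recorded and unrecorded history

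The estimate is the Mantel-Haenszel risk ratio stratified by recorded history.

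**3. One case worked through** (10%, odds ratio 0.25, risk ratio 5, 50% recorded, no true effect), per 10,000 patients, with risks in units of the baseline risk:

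- No history: 7,200 treated, 1,800 untreated. With history: odds 4 × 0.25 = 1, so 500 treated and 500 untreated; half of each (250) is unrecorded.
- Stratum without a record: treated (7,200 + 5 × 250)/7,450 = 1.134; untreated (1,800 + 5 × 250)/2,050 = 1.488; ratio 0.762.
- Stratum with a record: ratio 1.
- Pooled: (8,450 × 2,050/9,500 + 1,250 × 250/500) / (3,050 × 7,450/9,500 + 1,250 × 250/500) = (1,823.4 + 625)/(2,391.8 + 625) = 0.812.

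**4. Range over the assumed inputs.** The bias multiplies the true ratio.

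| Share recorded | True 1.00 | True 1.10 | True 1.20 |
|---|---|---|---|
| 50% | 0.81–0.97 | 0.89–1.06 | 0.97–1.16 |
| 80% | 0.92–0.99 | 1.01–1.08 | 1.10–1.18 |
| 100% | 1.00 | 1.10 | 1.20 |

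**5. Dependence on the assumptions.**

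- *Share treated.* At 50% recorded, the worst null estimate moves from 0.81 (80% treated) to 0.84 (50% treated) and 0.87 (20% treated).
- *Prescribing depends only on recorded history.* A true 1.00 stays 1.00 and a true 1.20 stays 1.20, for every combination at 50% and at 80% recording.
- *History encourages treatment* (odds ratio 1.5 to 2, 50% recorded). A true null is estimated as 1.02 to 1.09.
- *A milder set-up.* With history in 3% to 10% of each group, groups differing by 2 to 5 points, risk ratio 2 to 5 and 50% recorded, the bias factor is about 0.92–0.99 or 1.01–1.08.

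**6. Consequence at 4,634 events.** For the mildest case at 50% recording in step 4 (factor 0.965), ln(0.965)/0.0294 = −1.21. A true null is then rejected about 23% of the time. For a true 1.10, ln(1.0615)/0.0294 = 2.03, so power is about 53% instead of 90%.

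**The case against.** The best case against the point is about scope. The quoted sentence stands in a paragraph on deriving models for use in primary care, and deriving is the protocol's word for Aim 1. The wording on the propensity score is open, and the sources of individual covariates could be left to an analysis plan that is not shown. This stands in part: the sentence is no error for Aims 1 and 2. But the covariate row expressly includes predictors of treatment, the Aim 3 text uses the same word for the propensity inputs, and the open wording names no HES source. A source has been stated, so this is more than a detail left open.

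The protocol also has safeguards. The propensity models may be refined if they disagree with the instrumental variable analysis, but that happens only after results are seen. The negative controls (bowel cancer and COPD) aim at general ill health and lifestyle rather than at previous falls or bleeds. The planned sensitivity analyses change the source of outcomes, not of covariates.

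A reader might infer several stronger things that the documents do not support:

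- *That all covariates come from primary care alone.* Ethnicity may come from HES and deprivation from a linked index.
- *That previous events are the strongest confounder.* The documents rank none and give no prevalence or association.
- *That half of previous events are missed.* The 50% is an upper figure for one outcome, and the same passage calls co-morbidity recording consistent. Falls and bleeds are acute events and so resemble the former, but their recording rate is not given.
- *That every estimate is drawn towards safety.* Step 5 shows nil or reversed bias under other assumptions. A GP who is unaware of an event cannot be influenced by it.
- *That the pre-index records are certainly in hand.* The stated window is after the index date; look-back is implied only by the use of HES for previous CVD.

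**Conclusion.** The mismatch of sources holds for Aim 3. Previous adverse events, as the text stands, are covariates from primary care codes, while the same kinds of event are outcomes from HES and ONS, and the protocol itself accepts that a single source can miss acute events. To the extent that prescribing responds to history the GP did not code, the propensity and multivariable models adjust incompletely.

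The size cannot be fixed from the documents. It runs from no bias to a null estimated as 0.81 under the assumed inputs, and to 1.09 in the other direction. Part of that range is as large as the 10% effect of interest or larger, and part is minor. The point is worth correcting because the better definition is cheap, not because a bias of known size has been shown. Aims 1 and 2 are unaffected.

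**What to change.** - Keep predictors from primary care for Aims 1 and 2, and say that the quoted sentence applies to them.
- For Aim 3, define previous adverse events and previous acute CVD events from primary care or HES inpatient records dated before the start of exposure, using the outcome code lists. Use these variables in the propensity and multivariable models.
- Report the primary-care-only definition as a sensitivity analysis. The difference shows how much the choice of source matters.
- In Planned use of linked data, extend the stated use of HES to admissions before the index date.

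The cost is a few sentences in the protocol, some extra data preparation, and confirmation that the HES extract covers the pre-index period. HES Admitted Patient Care is already requested, and defining previous CVD from it already needs earlier admissions.

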| Study Type Hypothesis testing |
| Study Design Longitudinal cohort study |
| Feasibility counts There are approximately 5.5 million patients in England, aged 40+ and with up to standard registration for a period between 1/1/1998 to 31/12/2017 in the CPRD GOLD. Restricting to English practices (linked to HES and ONS) and only including patients fulfilling the eligibility criteria listed below, the expected population is approximately 3.3 million and out of these we expect 216,000 fall events, 230,000 myopathy/muscle pain events and 1,200 intracranial haemorrhage events. |
| Sample size considerations We have based our sample size calculation on the least common of the primary outcomes listed above (intracranial haemorrhage), and used the method developed by Riley *et al.,*^40^ to minimise the potential for overfitting and ensure precise estimates of key parameters. A sample size of approximately 80,000 patients is required for the development of a clinical prediction rule for this outcome, assuming an event rate of 24.6 per 100,000 person years,^41^ a median follow up of 7 years,^42^ a conservative estimate of Nagelkerke’s R^2^ statistic of 0.15 and a maximum number of 40 parameters per model.  Feasibility counts showed that this sample size is adequate for the development of the prediction rules. Since Intracranial bleeding is the rarest of the primary outcomes to be studied, the sample size will be sufficient for all other outcomes of interest. For validation, Vergouwe *et al.,*^43^ consider at least 100 events per sample population to be “substantial” and we will comfortably exceed this in our validation cohorts for each outcome of interest.  For analyses using causal inference methods (propensity score matching and instrumental variable analysis), assuming clinically significant increased rate of each adverse event with treatment of 10%, and an event rate of at least 0.5% per year in the non-exposed group, approximately 88,380 patients (44,190 in each group) and 4,634 events will be required to accurately define the relationship between preventative treatment and adverse events, with 90% power and an alpha of 0.05. |

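### The matched Cox analysis bars adjustment for a confounder that is in the propensity score but still unbalanced after matching, and no stated step requires re-matching

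*Protocol*

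**What the plan says.** Under Data/Statistical Analysis, Aim 3, the Protocol states that "eligible patients will be matched 1:1 at the index date using propensity scores". The score comes from a logistic model: "Predictors of preventative drug prescription will be explored in a logistic regression model". Matched patients are then compared with Cox models, in which "hazard ratios will only be adjusted by factors unbalanced at baseline which are not already included in the propensity score model". Amendment 3 restates the Aim 3 text with the same rule.

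The covariates in Exposures, Outcomes and Covariates, described there as predicting outcome, treatment or both, are "Age, sex, BMI, blood pressure, cholesterol, HbA1c, other prescribed medications, co-morbidities, social deprivation, previous adverse events, frailty and proximity to death".

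Aim 3 contains one refinement step. It applies when the matched and instrumental variable results differ: "If this is the case, these models will be refined with additional factors to achieve better adjustment and matching".

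Amendment 2 adds a multivariable Cox analysis adjusted for pre-specified confounders, and separates score adjustment from score matching. It does not alter the adjustment rule for the matched model.

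**The concern.** Entering a variable in a logistic propensity score does not guarantee that it is balanced in the matched sample. Balance also needs an adequate functional form and close matches. The rule allows adjustment for an unbalanced variable that was left out of the score and refuses it for one judged important enough to go in. If the score holds the main measured confounders, these are the variables for which the outcome model offers no second line of defence.

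The effect of interest is small, a 10% increase in rate, so a modest leftover imbalance in a strong prognostic factor could account for much of it. This bias does not shrink as the cohort grows.

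**Working it through.** **1. What the text allows when a score covariate stays unbalanced**

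- Adjust in the matched Cox model: barred by the rule, which requires a factor to be both unbalanced and outside the score.
- Refine the models: the stated trigger is disagreement with the instrumental variable result, not observed imbalance. The stated response is further factors, which need not correct a poorly specified term for a factor already in the score.
- Negative controls (Plan for addressing confounding): an apparent effect is attributed to something missing from the analysis, with an unmeasurable factor as the explanation. Residual imbalance in a measured covariate could be misread this way.
- Re-specify the score or re-match: neither forbidden nor required.

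**2. The Protocol's own sample size figure**

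Sample size considerations states "approximately 88,380 patients (44,190 in each group) and 4,634 events will be required", for a 10% increase, 90% power, alpha 0.05 and "an event rate of at least 0.5% per year in the non-exposed group".

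Freedman, two-sided: events = (1.960 + 1.282)² × [(1 + 1.10)/(1.10 − 1)]² = 10.507 × 441 = 4,634, which matches.

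Patients: taking 10 years (inferred; 1, 5 and 7 years do not reproduce the figure), unexposed risk = 0.5% × 10 = 5%, and exposed risk = 1 − 0.95^1.1 = 5.486%. N = 4,634 / [(0.05 + 0.05486)/2] = 88,384, against 88,380 stated. The figure does not depend on the adjustment rule.

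**3. Size of the bias for a given residual imbalance**

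Assumptions, because the Protocol gives no residual imbalance or confounder strength: a true hazard ratio of 1.00; a residual standardised mean difference (SMD) of 0.02, 0.05 or 0.10 in one continuous confounder; and a confounder hazard ratio of 1.5, 2.0 or 2.5 per SD.

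ln(spurious HR) ≈ SMD × ln(HR per SD). Example: 0.10 × ln 2.0 = 0.0693, so the HR is 1.072.

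For the false-positive rate at 4,634 events, SE = √(4/4,634) = 0.0294 and z = ln(HR)/SE. The rate is Φ(z − 1.96) + Φ(−z − 1.96). In the example z = 2.36, which gives 0.655.

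| Residual SMD | HR 1.5 per SD | HR 2.0 per SD | HR 2.5 per SD |
| --- | --- | --- | --- |
| 0.02 | 1.008 (0.059) | 1.014 (0.076) | 1.018 (0.096) |
| 0.05 | 1.020 (0.106) | 1.035 (0.218) | 1.047 (0.345) |
| 0.10 | 1.041 (0.281) | 1.072 (0.655) | 1.096 (0.877) |

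Entries are the spurious HR, with the two-sided false-positive rate in brackets.

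**4. A case where matching works well**

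Twelve simulated data sets used caliper matching, a mildly misspecified score, a confounder HR of 2 per SD and a true HR of 1.00. The mean residual SMD was 0.015. The mean HR was 1.000 without covariate adjustment and 0.985 with it. The formula in step 3 gives 0.015 × ln 2 = 0.0104, an HR of 1.010, so the expected bias was about 1%. No Monte Carlo error was recorded, so the gap between 1.000 and 0.985 should not be read as favouring either estimate. The scenario shows only that little is at stake when matching is close.

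**The case against.** The strongest reply is that the rule restricts one tool only. Re-specifying the score and re-matching is the usual first response to imbalance, and nothing forbids it. The reference to unbalanced factors also implies that balance will be examined. A reader might infer that residual imbalance must stay in the hazard ratio; the text does not go that far. What stands is that nothing requires the other remedy.

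Second, the matched estimate does not stand alone. A reader might infer that Aim 3 as a whole is exposed. Amendment 2 does not support that: it adds multivariable and score-adjusted analyses and runs the subgroup analyses by score adjustment only. Amendment 3 restates Aim 3 without these analyses, but it presents itself as adding exploratory work, so I read them as still planned. They limit the consequence without repairing the matched analysis.

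Third, about 3.3 million eligible patients are expected, so close matches may be plentiful and residual differences small. This is fair, and the bias in the table is conditional for that reason.

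Fourth, adjustment has a price. The hazard ratio becomes conditional instead of marginal and relies on the outcome model. Both points are correct. The first matters little at the roughly 5% ten-year risk implied by the sample size.

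Fifth, the contents of the score are not fixed, so one cannot say that age, frailty or blood pressure is certainly caught by the rule. That is right; the rule catches whichever factors are entered. Calipers and balance thresholds may sit in an analysis plan that is not shown, and their absence is no part of this point. The adjustment rule is different: the Protocol states it, and a plan that adjusted for score covariates would contradict it.

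**Conclusion.** The point holds for the matched Cox analysis and should be corrected. The Protocol fixes a rule that blocks a direct remedy for measured imbalance in score covariates and requires no other.

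Under the assumptions in the working, the spurious hazard ratio runs from about 1.01 (SMD 0.02, HR 1.5 per SD) to about 1.10 (SMD 0.10, HR 2.5 per SD). The upper end nearly equals the 10% effect the analysis is sized for. These figures show sensitivity and do not predict the bias: the documents do not show that such imbalance will occur, and close matching could make the effect negligible. No sample size figure is affected.

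**What to change.** In Data/Statistical Analysis, Aim 3, and in its restatement in Amendment 3, delete the closing clause that limits adjustment to factors outside the score. State instead that the matched Cox model adjusts for the pre-specified key confounders whether or not they are in the score, with robust standard errors for matched pairs. At a minimum, allow adjustment for any of them still unbalanced after matching. Routine adjustment is preferable: a trigger set at SMDs above 0.1 would leave the 0.10 row of the table uncorrected. Report the unadjusted matched hazard ratio alongside, so that readers can see the marginal estimate and how far it depends on the outcome model.

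The cost is one sentence in two places. The covariates are already planned data, and the sample size stays at 4,634 events and 88,380 patients.
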